##### Physical activity

Daily physical activity is measured with The Short Questionnaire to Assess Health Enhancing Physical Activity (SQUASH). The SQUASH assesses activities across 4 domains: 1) commuting activities (walking and cycling to/from work), 2) physical activity at work, 3) household activities and 4) leisure time activities (walking, cycling, gardening, chores and sports). Participants are asked to report the number of days per week spent on each activity during an average week in the past month, as well as the number of minutes per day and the intensity of each activity. The SQUASH is a fairly reliable (spearman's correlation coefficient = 0.58) and reasonably valid (spearman's correlation coefficient = 0.45) questionnaire [63]. Total levels of daily physical activity are assessed by two items on the number of days per week moderate intensity activities are performed (such as walking and cycling) for at least 30 minutes (this can be built up by blocks of 10 minutes) and how often per week vigorous intensity leisure time activities ("which make you sweat") are performed during 20 minutes. These items relate to international physical activity guidelines [57] as well as to the Dutch guidelines [64].

##### Dietary behaviour

Dietary behavior is operationalized as the intake of fruit, vegetables, fruit juice and snacks. These items were selected from the validated Short Fruit and Vegetable questionnaire (validity r = 0.50) [65] and the Fat list (validity r = 0.70) [66]. The number of days per week and the number of daily servings of fruit, vegetables and fruit juice is measured with five items on citrus fruit, other fruits, cooked vegetables, raw vegetables and fruit juice. The consumption of energy dense snacks is assessed by the number of days per week and the number of servings per day in 7 categories (peanuts, chips, cakes, candy bars, biscuits, other cookies and fries). Cut-off points for each behavior are adapted from recommendations of the National Nutrition Centre (The Hague, The Netherlands).

#### Secondary outcome measures

##### Sedentary behaviour

*S*edentary behavior is specified for work and for leisure time. Sedentary behavior at work is asked as the number of minutes per day spent on computer use, meetings and other activities. Leisure time sedentary behavior is asked as the number of minutes per day spent on watching tv, computer use and other activities. Answers are specified for week days and weekend days [67]. Additionally, total duration of sedentary behavior is asked per week as well as per weekend day during the last 7 days (IPAQ).

##### Determinants of behavior change

Based on the TPB, attitude, subjective norm, perceived behavioral control and intention are included on a 5-point Likert scale for physical activity, dietary behavior and watching one's weight [55]. Additionally, 3 items on barriers and 4 items on habit strength are added [46]. Motivational stage of change, based on PAP-M, is assessed for cycling to work, physical activity at work, leisure time physical activity, fruit consumption, snack consumption and watching one's weight [39].

##### Weight-related factors

Body weight and body height are measured with the participants standing without shoes and heavy outer garments. Weight is measured to the nearest 0,5 kg. Height is measured to the nearest 0,1 cm. Participants are asked to push their heels softly to the wall, or the back of stadiometer [62]. BMI is calculated from measured height and weight as kg/m^2^.

##### Health-related factors

Systolic and diastolic blood pressure (in mmHG) are measured in a seated position, after several minutes of rest. OPs are asked to follow the standard Dutch protocol for blood pressure measurements [68]. Total serum cholesterol is measured, and if feasible for OPs, HDL and LDL cholesterol are measured as well (mmol/l). As OPs apply the guideline during their daily practice, the type of instruments used for blood pressure and cholesterol measurements may vary between OPs. The type of instruments used is asked retrospectively, and OPs are requested to use the same instruments throughout the trial.

Cardiovascular disease risk profile is calculated using the European Systematic Coronary Risk Evaluation instrument (SCORE) based on systolic blood pressure (mmHG), cholesterol levels (mmol/l) gender, age and smoking status [69]. Quality of life is measured by the validated EuroQol [70]. Presence of chronic disease and medication use are asked for hypercholesterolemia, hypertension, angina, heart disease, myocardial infarct, COPD, arthritis, cancer, depression and diabetes.

##### Work related factors

Productivity and absenteeism are measured by the HPQ. In the HPQ, work productivity is conceptualized as a measure of actual performance in relation to possible performance (i.e. presenteeism) [71]. Productivity is assessed with two items, measuring absolute and differential productivity (i.e., productivity compared with others). Absenteeism is measured as the absolute number of workdays missed in the past 4 weeks because of problems with physical or mental health. The HPQ shows good concordance with employer records of work absence and work productivity [72,73].

#### Process evaluation

The process evaluation will assess eight aspects after the intervention period at 6 months by questionnaire and focus group interviews: context (organizational characteristics that affect the intervention), recruitment (sources and procedures used to recruit OPs and employees), reach (attendance rates of employees), dose delivered (the amount of intervention components actually delivered by the OP), dose received (the extent to which employees use materials or components recommended by program), participant's attitudes (the OPs and employees attitudes toward the quality of the intervention in terms of credibility and usefulness), fidelity (the extent to which the intervention was delivered as planned), and the link between results and process (to explain possible success or failures of the intervention) [74,75]. Moreover, OPs and workers are asked to rate the intervention with an overall score on a scale 1-10. Regarding fidelity, the extent to which OPs adhere to the guideline is assessed with performance indicators. Additionally, the OPs competence in behavior change counselling is assessed by rating three taped counselling sessions with the behavior change counselling index [76]. From each tape 10 minutes are randomly selected and scored by the MI trainer, who then provides feedback to the OPs. The behavior change counselling index shows acceptable levels of validity, reliability and responsiveness [76].

#### Economic evaluation

An economic evaluation will be conducted alongside the trial and include a cost-effectiveness analysis and a cost-utility analysis. Both analyses will be performed from a societal perspective and a company perspective. The time horizon will be 18 months, similar to the trial. The analysis will be performed according to the intention-to-treat principle. From the societal perspective, in the cost-effectiveness analysis the difference in incremental costs (in €) between the conditions will be related to the difference in waist circumference (in % change) between the intervention and control group. The costs include intervention costs (costs that are directly related to the intervention, such as the costs of training OPs and costs of intervention materials), direct health care costs (for example, costs of physiotherapy and hospitalisation) and indirect health care costs (such as costs for a healthy lifestyle, such as sports contribution fees and sports clothing). Costs will be valued using Dutch guideline prices for economic evaluation. With respect to the company perspective, the costs of the intervention and other costs related to the company will be included (such as reduced productivity and absenteeism) and compared to the difference in waist circumference (in cm) between the conditions. Absenteeism and productivity are measured every 3 months with the HPQ using cost-diaries [73].

The cost-utility analysis will focus on the difference in costs (in €) between the conditions per QALY (Quality Adjusted Life Year) gained. Utilities will be measured using the social tariff of EuroQol with Dutch reference values. Bootstrapping will be used for pair-wise comparison of the mean differences in costs between the two groups. Confidence intervals (95%) will be obtained by bias corrected and accelerated bootstrapping. Cost-effectiveness and cost-utility ratios will be calculated by dividing the difference in the mean costs between the study groups by the difference in the mean effects. Acceptability curves will be calculated, showing the probability that the guideline is cost-effective at a specific ratio. Furthermore, sensitivity analyses will be performed to assess the robustness of the results. All analyses will be performed using SPSS 15.0 (SPSS Inc. Chicago, Illinois, USA).

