#### Study design

OPs were randomly assigned to the intervention or control condition by an independent researcher using Random Allocation Software (version 1.0, Isfahan University of Medical Sciences, Iran). Randomization of OPs took place before the baseline measurement, as the first counseling session of the intervention group took place directly after the baseline measurement. OPs in the intervention group were trained during two days in the guideline and associated intervention, including behavioral change counselling by a professional trainer. OPs in the control group were asked to provide care as usual. OPs were asked not to reveal their condition to participating workers. The study protocol was approved by the Ethics Committee of the VU University Medical Center.

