#### Sample size

The sample size was calculated according to the number of cases needed to identify an effect on waist circumference. Waist circumference was chosen over BMI as it is a more sensitive indicator of abdominal fat mass [61]. A previous study indicated that a difference in waist circumference of 1,5 cm between the intervention and control condition may be clinically relevant [43]. In an intention-to-treat analysis, 175 workers per condition are needed to detect a relative difference of 1,5 cm (standard deviation 4,5 cm) in waist circumference with a power of 80% and an alpha of 5%. As workers are clustered within OPs we adjusted for dependence of measurements with an intraclass correlation of 0.20. Taking a loss to follow-up of 20-40% into account among workers and OPs until the final measurement, the initial study population should consist of approximately 300 workers among 10 OPs in each study group (figure 4).

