#### Data analysis

The effectiveness of the weight gain prevention guideline will be analyzed after 6 months (short term) and after 18 months (long term) by means of multilevel analyses. Multilevel analyses accounts for the clustering of observations of workers within the same OP, as well as repeated measurements within one worker. Due to randomization at the OP level, short term data will be analyzed with two levels: 1. worker and 2. OP. Long term data will be analyzed with three levels: 1. time (3 follow-up measurements at 6, 12 and 18 months), 2. worker and 3. OP. Both crude and adjusted analyses will be performed. The multilevel analyses using the follow-up measurement (i.e. 6 months) as dependent variable will be adjusted possible confounders such as, gender, age and education. These variables will also be checked for effect modification. The long-term effect of the intervention will be analyzed using all three follow-up measurements (i.e. 6, 12 and 18 months) adjusted for possible confounders. Effect modification is checked. All statistical analyses will be performed according to an intention-to-treat principle. The investigator analysing the data is blinded to the randomization. A two tailed significance level of p < 0.05 is considered statistically significant. Analyses will be performed with SPSS 15.0 (SPSS Inc. Chicago, Illinois, USA) and MLwiN for multilevel statistical analyses.

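### The economic evaluation makes no provision for clustering by occupational physician (OP), so on its ordinary reading it understates uncertainty in incremental costs, effects and cost-effectiveness

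*Protocol article*

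**What the plan says.** Under Study design, the unit of allocation is the OP: "OPs were randomly assigned to the intervention or control condition by an independent researcher". Under Sample size, the target is "approximately 300 workers among 10 OPs in each study group", and the dependence is acknowledged: "we adjusted for dependence of measurements with an intraclass correlation of 0.20".

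Under Data analysis, effectiveness is estimated by multilevel models with OP as a level, in MLwiN alongside SPSS: "Multilevel analyses accounts for the clustering of observations of workers within the same OP".

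Under Economic evaluation, the method is given in some detail. The cost comparison is described thus: "Bootstrapping will be used for pair-wise comparison of the mean differences in costs between the two groups". The type of interval is fixed as well: "Confidence intervals (95%) will be obtained by bias corrected and accelerated bootstrapping". Ratios are the difference in mean costs divided by the difference in mean effects, acceptability curves follow, and "All analyses will be performed using SPSS 15.0". That section mentions no OP level, no cluster resampling and no multilevel model. It does not name the unit that is resampled.

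**The concern.** A bootstrap gives valid intervals only if it resamples in a way that mirrors how the data vary. Here 20 OPs were allocated and the workers of one OP may resemble each other. The bias-corrected and accelerated (BCa) adjustment deals with bias and skewness in the bootstrap distribution. It does nothing for dependence between workers of the same OP.

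The section therefore sits badly with its neighbours. Waist circumference would carry OP-level uncertainty in the effectiveness analysis, yet could lose it as the denominator of the cost-effectiveness ratio. Costs may cluster too: each OP serves particular companies, so absenteeism and productivity can share an employer.

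At stake are the precision of the cost difference and the probability read from the acceptability curve. Under Phase 3, the cost-effectiveness result is one of the inputs for adapting the guideline before national dissemination.

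**Working it through.** **The plan's own figures.** The Economic evaluation section states no sample size, ICC or precision, so it offers no figure to reproduce. The only related figure is the 175 workers per condition for waist, based on a "relative difference of 1,5 cm (standard deviation 4,5 cm) in waist circumference with a power of 80% and an alpha of 5"%. The two-sided formula gives n = 2 × (1.96 + 0.842)² × (4.5/1.5)² = 141.3, so 142 per arm before any clustering. The 175 is not reproduced from those inputs; that is a separate matter and does not bear on the result below.

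**Inputs.**
- OPs per arm: 10; workers per arm: about 300, so 30 per OP at the start (Sample size).
- Loss to follow-up: 20–40% (Sample size). At 40%, 300 × 0.6 / 10 = 18 workers per OP; at 20%, 24 per OP, if all OPs stay.
- The economic horizon is 18 months, so 18 to 24 per OP is the relevant range; 30 assumes no loss.
- ICC: 0.20, stated for waist. None is given for costs or QALYs, so 0.01 to 0.20 is an assumed range.

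**Formulae.** With m workers per OP:
- design effect DE = 1 + (m − 1) × ICC
- factor by which the standard error is understated = √DE
- actual coverage of a nominal 95% interval that ignores OP = 2Φ(1.96/√DE) − 1

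For m = 18 and ICC 0.20: DE = 1 + 17 × 0.20 = 4.40; √DE = 2.10; 1.96/2.10 = 0.93; coverage = 65%.

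| ICC | DE, m = 18 | SE factor, m = 18 | Coverage, m = 18 | Coverage, m = 24 | Coverage, m = 30 |
|---|---|---|---|---|---|
| 0.01 | 1.17 | 1.08 | 93% | 92% | 92% |
| 0.05 | 1.85 | 1.36 | 85% | 82% | 79% |
| 0.10 | 2.70 | 1.64 | 77% | 72% | 68% |
| 0.20 | 4.40 | 2.10 | 65% | 59% | 55% |

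**Check by simulation.** Skewed worker-level data were generated with no true difference, 10 OPs per arm and 18 workers per OP, in 600 replicates, using percentile rather than BCa intervals.

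| ICC | Coverage, workers resampled | Coverage, whole OPs resampled | Bootstrap probability of a cost difference above 0.95 or below 0.05 (workers resampled) |
|---|---|---|---|
| 0.01 | 93% | 92% | 13% |
| 0.05 | 82% | 90% | 25% |
| 0.10 | 76% | 92% | 32% |
| 0.20 | 64% | 93% | 44% |

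The last column should be about 10% when there is no difference. It shows the same fault as a curve that is too steep: the analysis reports near-certainty too often.

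With 30 workers per OP, resampling whole OPs also covered 90–93%. The shortfall from 95% comes from having only 10 OPs per arm. In a separate simulation at 18 workers per OP, a t interval on OP means with 18 degrees of freedom covered about 95% at every ICC in the table.

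**The case against.** The strongest reply is that the article never says workers are resampled. It is a condensed report, the full protocol or an economic plan may name the unit, and the authors plainly know about the clustering. Naming SPSS alone, where the effectiveness analysis adds MLwiN, is suggestive and no more. This stands in part: a reader might infer that the plan commits itself to resampling workers as independent, and the text does not go that far. But the section is not silent on method. It fixes the comparison, the interval type, the ratio and the software, and none of these accommodates the OP. Followed as written, it gives the worker-level analysis.

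Second, the bootstrap sentence concerns costs, and the section does not say how uncertainty in the effects is obtained. That is correct. The ratio is nevertheless defined from differences in mean effects, with no link to the multilevel estimates.

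Third, 0.20 was assumed for waist, and no ICC is given for costs or QALYs. A reader might infer that the 65% figure describes the cost intervals. The document does not support that; at ICC 0.01 the loss is small.

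Fourth, a reader might infer that the cost-effectiveness ratio is itself wrong. Clustering alters the uncertainty around the ratio, not the point estimate defined in the section.

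Finally, cost-effectiveness is an additional assessment, and the adaptation of the guideline also rests on effectiveness, process results and expert advice. This limits the severity.

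**Conclusion.** The point holds as an inconsistency. The economic analysis is specified without the OP level that the allocation requires and that the sample size and effectiveness analysis both recognise.

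If workers are resampled individually and the ICC is positive, the uncertainty around incremental costs, effects and the ratio is understated and the acceptability curves are too steep. At 18 workers per OP, the standard error is too small by a factor between 1.08 (ICC 0.01) and 2.10 (ICC 0.20). The conclusion rests on three assumptions: worker-level resampling, which is the ordinary reading rather than stated text; an ICC for costs and QALYs that the document does not supply; and roughly equal numbers of workers per OP.

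Severity: should be fixed. The analysis is secondary, and the primary effectiveness inference is not affected.

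**What to change.** State in the Economic evaluation section that costs and effects are analysed jointly with OP as the cluster, by one of two routes:
- a bivariate multilevel model for costs and effects with an OP random effect; or
- a two-stage cluster bootstrap with shrinkage that resamples OPs within arm and keeps each worker's costs and effects together.

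Derive the confidence intervals, the cost-effectiveness plane and the acceptability curves from that analysis, and name the software that will do it.

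With 10 OPs per arm, a plain bootstrap of whole OPs under-covers slightly (about 90–93% in the simulation), so the multilevel model or a small-sample correction is preferable.

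The cost is a few sentences of analysis text, some programming beyond the standard SPSS bootstrap, and wider intervals. No new data and no change in trial conduct are needed.

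### The economic ratios are defined from differences in means, with no link to the multilevel models and no baseline-utility covariate; read plainly, this gives away precision, chiefly in the QALY difference

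*Protocol article*

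**What the plan says.** In Methods, Phase 2, Economic evaluation, the ratios are "calculated by dividing the difference in the mean costs between the study groups by the difference in the mean effects". For uncertainty, "Bootstrapping will be used for pair-wise comparison of the mean differences in costs between the two groups". On utilities, the section says "Utilities will be measured using the social tariff of EuroQol with Dutch reference values"; it does not say how QALYs are built from them or whether baseline utility is a covariate. The waist effect has two scales. In the societal analysis costs "will be related to the difference in waist circumference (in % change) between the intervention and control group"; from the company perspective costs are "compared to the difference in waist circumference (in cm) between the conditions". On software, the section says "All analyses will be performed using SPSS 15.0".

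The next section, Data analysis, takes another route for effectiveness: "Multilevel analyses accounts for the clustering of observations of workers within the same OP, as well as repeated measurements within one worker". It plans crude and adjusted analyses, gives gender, age and education as example confounders, takes the follow-up measurement as the dependent variable at 6 months, and adds MLwiN to the software. It does not name the baseline value of the outcome as a covariate.

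EuroQol is listed under Health-related factors, and the Abstract places measurements at baseline and at 6, 12 and 18 months.

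**The concern.** The authors name multilevel models, covariates and the multilevel software where they intend them. Their absence from the Economic evaluation section makes simple differences between arm means the natural reading. Two things follow from that reading.

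First, QALYs. If they are the area under the utility curve from baseline to 18 months, baseline utility is part of each worker's QALY. Only 20 OPs are randomised, so some baseline difference in EuroQol between the arms is to be expected, and an unadjusted difference counts it as QALYs gained or lost. QALY differences from a prevention programme may be small. Noise in a small denominator moves the ratio and the acceptability curve easily.

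Second, waist. A pooled arm mean weights each OP by the number of workers measured, whereas a multilevel estimate weights OPs more equally. The Discussion notes that OPs recruit in different ways, so unequal cluster sizes are plausible. The waist effect in the ratio could then differ from the one in the effectiveness analysis.

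Phase 3 says the guideline will be adapted in the light of the cost-effectiveness results, so the choice of estimate has a practical consequence.

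**Working it through.** The plan gives no figure for this point, so there is none to reproduce. The check is of size.

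**QALY difference**

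From the Sample size section: 175 workers per arm and 10 OPs per arm, taken here as completers, hence 17.5 per OP. From the Economic evaluation section: an 18-month horizon. Assumed, because the documents give no values: utility SD 0.10-0.18; ICC of utility 0-0.03; within-worker correlation r = 0.5-0.7, equal between all time points and the same at OP level; QALY by the trapezoid rule.

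1. Trapezoid weights at 0, 6, 12 and 18 months are 0.25, 0.5, 0.5, 0.25 years (sum 1.5, sum of squares 0.625).
2. Variance of one worker's QALY, in units of SD²: 0.625 + (1.5² − 0.625)r = 0.625 + 1.625r. This is 1.4375 at r = 0.5 and 1.7625 at r = 0.7.
3. Covariance with baseline utility: 0.25 + 1.25r, which is 0.875 and 1.125.
4. Variance left after adjustment: 1.4375 − 0.875² = 0.672, and 1.7625 − 1.125² = 0.497.
5. Standard error of an arm difference: SD × √variance × √(2·DE/175), with DE = 1 + 16.5 × ICC. For ICC 0, DE = 1 and the last factor is 0.107. For ICC 0.03, DE = 1.495 and it is 0.131.

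| Quantity | Smallest | Largest |
|---|---|---|
| SE unadjusted | 0.10 × √1.4375 × 0.107 = 0.013 | 0.18 × √1.7625 × 0.131 = 0.031 |
| SE adjusted | 0.10 × √0.497 × 0.107 = 0.0075 | 0.18 × √0.672 × 0.131 = 0.019 |
| SD between the two estimates | 0.10 × 0.875 × 0.107 = 0.009 | 0.18 × 1.125 × 0.131 = 0.026 |

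Simulation gives the same ranges with slightly wider ends: 0.013-0.032, 0.007-0.019 and 0.009-0.027. The cut in standard error is 1 − √(0.672/1.4375) = 32% at r = 0.5 and 1 − √(0.497/1.7625) = 47% at r = 0.7, or about 30-48% by simulation. The percentage depends on r, not on the assumed SD.

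**Waist difference**

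From the Sample size section: SD 4.5 cm, ICC 0.20, target 1.5 cm, 10 OPs per arm. Assumed: ICC also at 0.05-0.10; coefficient of variation (CV) of cluster size 0.3-0.7; mean 17.5 or 30 workers per OP.

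1. Standard error with equal clusters, ICC 0.20: DE = 1 + 16.5 × 0.20 = 4.3, and 4.5 × √(2 × 4.3/175) = 1.0 cm.
2. With unequal clusters the pooled design effect is 1 + ((CV² + 1) × 17.5 − 1) × ICC. At CV 0.7 and ICC 0.20 this is 1 + (1.49 × 17.5 − 1) × 0.20 = 6.0, a standard error of 4.5 × √(2 × 6.0/175) = 1.18 cm.
3. Simulation of the pooled difference against the random-intercept weighted difference, 17.5 workers per OP: at CV 0.7 and ICC 0.20 the standard errors are 1.17 and 1.05 cm (11% apart; 13% with 30 per OP). At CV 0.3 and ICC 0.05 they are 0.66 and 0.66 cm (about 1% apart).
4. SD of the difference between the two estimates within one trial: from about 0.09 cm (CV 0.3, ICC 0.05) to about 0.5 cm (CV 0.7, ICC 0.20). Both estimates are centred on the true effect.

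**The case against.** The strongest reply is that the formula is the ordinary definition of an incremental ratio, which adjusted mean differences also satisfy. The section never says crude or unadjusted, and naming one software package does not exclude the multilevel estimates. On baseline utility it is silent, and a journal article commonly leaves such detail to a full analysis plan. This stands as far as certainty goes: the simple-means reading is natural but inferred. It does not remove the point, because the section does state an estimator and gives no sign that a model lies behind it.

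Three stronger conclusions are tempting and not supported.

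- *A reader might infer that the trial will report two conflicting waist effects.* The Data analysis section already plans crude and adjusted effects, and the economic section openly uses percentage change and centimetres. Several waist figures are planned.
- *A reader might infer that the ratios are biased, or rest on a clearly inferior waist estimate.* In the setting checked, both estimators are unbiased and the precision loss is small. The Data analysis model does not name baseline waist, whereas a percentage change already refers to baseline, so that model as written is not shown to be the more precise. Weighting workers equally is also defensible for a cost per worker.
- *A reader might infer that the cost-utility result will be driven mainly by baseline imbalance.* The share of variance due to baseline is 0.875²/1.4375 = 53% to 1.125²/1.7625 = 72%, but only under the assumed correlations and area-under-the-curve QALYs. It is chance variation, which an interval from resampling OPs would show.

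**Conclusion.** The point holds as a matter of precision and consistency. The plan as written gives up an available gain in the cost-utility analysis: a cut of about 30-48% in the standard error of the QALY difference, with the adjusted and unadjusted estimates differing by an SD of about 0.009-0.027 QALY. This rests on the plain reading of the formula, on area-under-the-curve QALYs, and on assumed utility SD, ICC and correlation; none of these QALY inputs is in the documents. For waist the loss is about 1-12%, and the reason to act is that the effect in the ratio should be traceable to a stated model. The documents do not show bias, and do not say that adjustment is excluded.

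**What to change.** In the Economic evaluation section, replace the differences in means by model-based differences:

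- **QALYs:** state how they are computed, and estimate the increment by a multilevel regression (worker within OP) of QALY on arm and baseline EuroQol utility.
- **Waist:** take the increment from an OP-level multilevel model with baseline waist as a covariate, on the scale used in each ratio.
- **Costs:** take the increment from an OP-level multilevel model.
- **Uncertainty:** refit all of these in each bootstrap sample, and form the ratios and acceptability curves from the refitted estimates.
- **Sensitivity analysis:** report the unadjusted ratios.

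The cost is a few sentences and some extra programming. No new data are needed, because baseline EuroQol and waist are within the planned measurements.
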